### Termination Criteria for the Whole Study

In case of serious safety concerns, the principal investigators could terminate or interrupt the study. If new information on the risk-to-benefit ratio of the intervention (including treatment or investigational processes) used in the study was obtained in the meantime, the principal investigators reserved the right to interrupt or terminate the project. In addition, premature termination of the study was possible if the principal investigators noticed that participant recruitment was insufficient and could not be accelerated through appropriate measures.

### Study Intervention

The main intervention was bread fortified with DRB. It is a commonly eaten grain and is safe for human consumption [14,50-54]. On the basis of measured composition, the main intervention had 18% of the flour (cereal weight) replaced with 18% of the flour (cereal) weight used in the placebo bread and provided 8 g (for female individuals) and 10.6 g (for male individuals) of total DF. Of the 8 to 10.6 g of DF in 3 to 4 slices of fortified bread, 2.2 g (for female individuals) and 2.9 g (for male individuals) were fiber from wheat, and 5.8 g (for female individuals) and 7.7 g (for male individuals) were from the DRB. The placebo was a matched commercial white toast bread without DRB, providing 2.7 g of DF for female individuals (3 slices) and 3.6 g of DF for male individuals (4 slices). Toast slices were chosen for this study to ensure that the production of DRB-fortified bread had a texture similar to that of the placebo white toast bread while providing the required DF content.

### Blinding and Allocation Concealment

Participants were not informed of the bread ingredients until the completion of the study data collection to maintain blinding. Analysts and researchers were blinded to the order of treatment that the participants received and to which group the participants were assigned during data collection and remained blinded until the statistical analysis of the primary outcome data was completed. The manufacturer of the bread was responsible for labeling both breads to maintain blinding of research team members. To further increase blinding, the manufacturer added colored malt to the placebo bread to make both breads visibly indistinguishable. Specified research team members were responsible for the randomization, enrollment, and data collection of participants; the handout of the intervention and placebo bread; and the management of the stock. Unblinding was only permissible once statistical analysis of the primary outcome data was completed.

### Randomization

One week before the first baseline visit, participants were randomly assigned in a 1:1 allocation using randomized permuted blocks (block size 4) to either DRB-fortified or placebo bread. Randomization was performed by drawing a folded note from a sealed opaque box.

### Measurements and Outcomes

#### Timing of Assessments

Upon enrollment, there were 5 clinic visits in total. Study assessments were conducted at baseline 1 (day 0 or week 1), postintervention assessment 1 (day 29 or week 5), baseline 2 (day 42 or week 8), postintervention assessment 2 (day 78 or week 12), and follow-up (day 91 or week 15). A total of 15 participants who were part of the Atmo substudy ingested capsules at 4 time points: baseline 1 (day 0 or week 1), postintervention assessment 1 (day 29 or week 5), baseline 2 (day 42 or week 8), and postintervention assessment 2 (day 78 or week 12).

#### Biological Measurements

##### Fecal Samples

###### Overview

The primary outcome was the differences in the relative abundance of a composite of selected key genera and species of the gut microbiota known to be involved in plant glycan metabolism or known to be modulated by the DRB-fortified bread (see the *Sample Size* section for more details) as compared with the placebo bread.

Once enrolled, participants received a posted cooler bag containing a fecal collection kit and ice pack. Participants collected a fecal sample into the provided fecal container 24 hours before their clinic visits at baseline, the postintervention time point of each phase, and follow-up. Participants were instructed to label the fecal container with the time and date collected and record it again on the bowel movement diary app. Participants had to refrigerate the collected fecal sample and transport it within 24 hours of sample collection in the provided cooler bag for each clinic visit. If participants could not provide a fecal sample 24 hours before, they were encouraged to collect and bring the sample in the cooler bag as soon as possible following their clinic visits.

In total, 5 aliquots (1 g each) of a fecal sample were frozen for microbial composition, gene abundance, and metabolite analyses. The samples were kept chilled until aliquoted in the laboratory. All aliquots were snap frozen in liquid nitrogen before storage at –80 °C until analysis.

###### Microbial Composition and Gene Abundances

Taxonomic composition and gene abundance of the fecal microbiome were assessed through shotgun metagenomics. Libraries for metagenomics sequencing of the extracted DNA were performed by Auckland Genomics at the University of Auckland, New Zealand. Microbial metagenomic libraries were then generated using the seqWell purePlex DNA library preparation approach. Briefly, genomic DNA was diluted to 5 ng/μL and then sheared and bar-coded with unique dual indexes using transposases to produce a library with fragment sizes of 300 to 1500 base pairs (bp). Libraries were pooled in batches of 24 samples and subjected to a paramagnetic bead-based cleanup. The DNA samples underwent quality control checks for purity and concentration using a bioanalyzer. The samples were shotgun sequenced using the Illumina NovaSeq 6000 platform using 2 × 150 bp paired-end sequencing at Novogene in Singapore.

The quality of the raw data was checked using FastQC (version 0.11.9; Babraham Bioinformatics) [55]. The Trimmomatic software (version 0.36; USADEL LAB) [56] was used for the removal of adapters and low-quality (Phred scores of <30) and short (<36 bp) sequencing reads. Read pairs were aligned to the human reference genome (RefSeq: GCF_000001405) using the “mem” algorithm of BWA (version 0.7.17-r1188) [57], and FASTQ files were generated from the unmapped sequencing reads using the “fastq” function of SAMtools (version 1.8) [58]. Read pairs were joined using PEAR (version 0.9.6) [59] with default settings. Read pairs that did not join were pasted together with a string of Ns using the “fuse” function from the BBMap package (version 38.22-0; Department of Energy Joint Genome Institute) [60]. Joined and fused reads from different lanes from the same sample were compiled into a final “clean” read sample file. Metagenomics functions were obtained through the “blastx” function of DIAMOND (version 0.9.22) [61], mapping the reads against the “nonredundant” National Center for Biotechnology Information database [62]. MEGAN (version 6; ultimate edition) [63] was used to assign putative functions to the alignment files produced by Diamond. This alignment was performed by [name] (statistician; AgResearch).

Differential relative abundance was performed using *DESeq2* in R (version 1.40.2; R Foundation for Statistical Computing). This package analyzes differential expressed taxa based on a negative binomial distribution. The effect of group was assessed by comparing between groups. The top 10 differentially abundant taxa were extracted based on adjusted *P* values for both baseline and postintervention assessments for each group. Taxa that changed within each group were identified by finding the set difference between the top taxa between baseline and the postintervention assessment. Log2FoldChange values were extracted for the identified changed taxa in each group [64]. Enrichment of functional gene attributes arranged hierarchically as level 1 (broadest level of function, eg, metabolism and cellular processes), level 2 (specific functions, eg, carbohydrate metabolism and amino acid metabolism), and level 3 (detailed pathways, eg, glycolysis and glycan degradation) were analyzed using the R package *Microbiome Multivariable Associations with Linear Models*, which uses general linear models that accommodate crossover designs [65]. Fixed effects included in the model were groups (DRB-fortified vs placebo bread).

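### Only human reads are removed before functions are assigned, so rice-bran DNA that survives into stool could be counted as microbial genes on the DRB bread in the secondary functional analysis

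*Protocol article*

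**What the plan says.** The Protocol article, under Microbial Composition and Gene Abundances, lists the pipeline in order and with software versions. After quality checks and trimming, "Read pairs were aligned to the human reference genome (RefSeq: GCF_000001405") and "FASTQ files were generated from the unmapped sequencing reads". Pairs were then joined or fused, and "Joined and fused reads from different lanes from the same sample were compiled into a final “clean” read sample file". The next step was a DIAMOND blastx search, "mapping the reads against the “nonredundant” National Center for Biotechnology Information database". Finally MEGAN "was used to assign putative functions to the alignment files produced by Diamond". No rice, wheat or other plant reference is subtracted at any step, and no restriction to bacterial or archaeal hits is stated.

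The same section tests functional attributes at three hierarchical levels, with bread as the only named fixed effect: "Fixed effects included in the model were groups (DRB-fortified vs placebo bread"). The Statistical Analysis Plan section describes the gene-level comparison as microbial and flags genes whose absolute log fold change exceeds 1.1. Hypotheses and Objectives assigns gene abundances to the fecal gut microbiota and lists them among the secondary aims.

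Under Study Intervention, "the main intervention had 18% of the flour (cereal weight) replaced". The fiber breakdown there attributes 5.8 g (female) or 7.7 g (male) per day to DRB. For the control, "The placebo was a matched commercial white toast bread without DRB".

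**The concern.** Stool contains DNA from the host, from microbes and possibly from food. The pipeline removes the host. It has no stated step for food, although the food is the treatment. Wheat is in both breads, so its reads largely cancel in the comparison. Rice bran is the designed difference between the breads, so any surviving rice DNA follows the bread within each participant.

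Randomization, blinding and the crossover do not remove such a signal. Comparing with baseline does not remove it either, because baseline samples precede the bread. False-discovery control does not help: the difference in reads would be real, and only its attribution to microbes would be wrong. At stake is whether a gene or pathway reported as a microbial response to DRB is partly the bran itself.

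**Working it through.** There is no figure in the article to reproduce on this point, so the check is a trace of the steps followed by a mixing calculation.

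**Trace.** Human reads are removed, all other reads are kept, the database has no stated taxonomic limit, functions are assigned to the alignments, and functions are compared by bread. Nothing elsewhere in the article describes a plant-read filter.

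**Inputs.** The article gives none of the three shares below; all are assumptions.
- f: net rice share of retained reads, DRB minus placebo. Assumed 0.1%, 1% and 5%.
- p: share of rice reads that carry the function. Assumed 1%.
- m: share of microbial reads that carry the function. Assumed 0.1%, 0.01% and 0.001%.

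**Formula.** Apparent DRB/placebo ratio with no true microbial change:

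[(1 − f)·m + f·p] / m = 1 + f·(p/m − 1)

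**Results**, as ratio (log2 ratio):

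| m | f = 0.1% | f = 1% | f = 5% |
|---|---|---|---|
| 0.1% | 1.009 (0.01) | 1.09 (0.12) | 1.45 (0.54) |
| 0.01% | 1.10 (0.14) | 1.99 (0.99) | 5.95 (2.57) |
| 0.001% | 2.00 (1.00) | 10.99 (3.46) | 50.95 (5.67) |

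Example: m = 0.01% and f = 1% give 1 + 0.01 × (100 − 1) = 1.99.

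For functions common in microbes the ratio stays close to 1. With m = p = 10% it is 1.00 at every f. With m = 1% and p = 2% it is only 1.05 at f = 5%.

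**Against the 1.1 threshold.** The base of the logarithm is not stated. Read as log2, the threshold is a ratio of 2^1.1 = 2.14. Solving 1 + f·(p/m − 1) = 2.14:
- m = 0.01%: f = 1.14/99, about 1.2%.
- m = 0.001%: f = 1.14/999, about 0.11%.
- m = 0.1%: f = 1.14/9, about 13%, outside the assumed range.

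**Primary composite.** The Sample Size section gives a mean of 28.3% and a target difference of about 6 points. If rice reads were in the denominator, the shift on DRB would be −28.3 × f:
- f = 0.1%: −0.03 points.
- f = 1%: −0.28 points.
- f = 5%: −1.4 points.

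The shift is downward on DRB, against the hypothesized increase.

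**The case against.** The strongest reply is that this rests on what a condensed article leaves out. MEGAN can separate reads by taxon, the stated target is the fecal microbiome, and a restriction to microbes may have been applied without being reported. The article also does not show that rice DNA survives defatting, baking and digestion in sequenceable amounts. Both points stand as limits on certainty. They do not remove the concern: the removal step, the database and the assignment step are all specified, and as specified they admit plant reads. If a restriction was applied, one sentence settles the matter.

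A reader might infer three stronger things that the document does not support.
- **That large, significant false differences will appear.** The size depends on three unknown shares, and no variance or test has been attached to them. Only the net rice difference counts, since wheat and rice in the background diet can occur on both breads.
- **That the carbohydrate and glycan pathways of main interest are compromised.** If these are common in microbes, as one would assume, the ratio stays near 1. The exposed functions are those that microbes rarely carry.
- **That the primary outcome is biased in a way that matters.** The article does not state the denominator. Even if it includes plant reads, the shift is probably small and could not create a false increase on DRB.

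**Conclusion.** The point holds for the secondary functional analysis. As described, the pipeline lets rice-bran DNA count as fecal-microbiota genes, and the error would track treatment. Whether it is material cannot be judged from the document. Under the assumed shares, ratios for functions at 0.01% to 0.001% of microbial reads run from about 1.1 to 51. Some pass the 1.1 threshold if it is read as log2, while common functions and broad categories barely change.

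For the primary composite the point is minor: 0.03 to 0.28 points at net rice shares of 0.1% to 1%, conditional on the denominator and toward the null. The 1.4-point figure needs a net share of 5%. The change is worth making because it is cheap and the bias it guards against is linked to treatment, not because harm has been shown.

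**What to change.** Before building the function and taxon tables, keep only reads that MEGAN assigns to Bacteria or Archaea. Subtracting rice and wheat reference genomes at the step that now removes human reads can be added. Use the retained reads as the denominator for relative abundance, and say so. All 15 taxa in the composite are bacterial or archaeal, so none is lost as a category.

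Report the plant-read fraction by bread as a check. Rice reads could reveal allocation, so fix the filter without reference to bread and tabulate the fraction after the permitted unblinding. If a microbial restriction was already in place, state it and report the fraction.

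The cost is one filter and a re-run on existing files, with no new samples. A small number of ambiguously assigned reads would be lost, and non-bacterial, non-archaeal microbes such as fungi would drop out of these tables.

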For the primary outcome, to determine the microbiome composite, the selected genera and species will be summed to give a composite relative abundance for each participant. Changes in the composite of the microbial taxa within and between groups will be assessed using the nonparametric Wilcoxon signed rank test. The statistical significance level is determined at *P*<.05, with a false discovery rate (FDR) of *P*<.10. A probable biological significance level (trend) is assumed at an unadjusted *P*≤.10. For other fecal microbiome measures, univariate and multivariate statistical analyses will be used to assess α- and β-diversity variations, individual relative abundance differences in taxa, and gene abundance differences between groups. Differences in α-diversity between baseline and the postintervention assessment and between groups after the intervention will be assessed using the nonparametric Wilcoxon signed rank test with continuity correction. The Benjamini-Hochberg method will be applied to control the FDR inherent in multiple-hypothesis testing for variables in the microbiome and metabolome analyses. The resulting adjusted *P* values will be computed to address the inflated type-I error rates associated with numerous comparisons. *P*<.05 and an FDR of *P*<.10 will be deemed significant, with a probable biological significant difference (trend) assumed at an unadjusted *P*≤.10.

Box plots will be created using *ggplot2* to compare groups for each Chao1 and Shannon Indexes. The permutational multivariate ANOVA and the analysis of dissimilarity functions will then be used to assess the statistical significance of microbial community composition between individuals. Analysis of dissimilarity uses permutation testing and provides statistical assessments and their significance using *F* tests based on the sequential sums of squares from the permutations to determine whether the observed differences in β-diversity are statistically meaningful. Microbial differential gene expression will be performed using quasi-likelihood *F* tests. This test provides stricter error rate control by accounting for the uncertainty in dispersion estimation. Genes with an absolute log fold change of >1.1 will be considered as differentially expressed.

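### Within-group taxon changes are declared by comparing two top-10 lists, which does not test change and has no error control

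*Protocol article*

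**What the plan says.** The Protocol article, section Microbial Composition and Gene Abundances, analyses taxa with DESeq2 in three steps.

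- A group comparison: "The effect of group was assessed by comparing between groups".
- A ranking step at baseline and at postintervention for each group: "The top 10 differentially abundant taxa were extracted based on adjusted" P values.
- A rule for within-group change: "Taxa that changed within each group were identified by finding the set difference between the top taxa between baseline and the postintervention assessment". Log2 fold changes are then extracted only for the taxa so identified.

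The section Statistical Analysis Plan sets the multiplicity rule: "The Benjamini-Hochberg method will be applied to control the FDR inherent in multiple-hypothesis testing for variables in the microbiome and metabolome analyses". Results at P<.05 with an FDR of P<.10 "will be deemed significant, with a probable biological significant difference (trend) assumed at an unadjusted" P≤.10. For genes it says "Microbial differential gene expression will be performed using quasi-likelihood" F tests, adding "This test provides stricter error rate control by accounting for the uncertainty in dispersion estimation", and then: "Genes with an absolute log fold change of >1.1 will be considered as differentially expressed".

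**The concern.** The second and third steps form a decision rule, and that rule never estimates or tests a change.

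1. It compares membership of two ranked lists. A taxon ranked 10th and then 11th counts as changed. A taxon whose abundance shifts strongly but which stays in both lists does not.
2. As written, adjusted P values serve only to rank. Ten top-ranked taxa exist whatever their P values are.
3. The Benjamini-Hochberg adjustment concerns differential abundance within one list. It gives no error rate for the statement that a taxon changed between two assessments.
4. Fold changes are extracted only for the selected taxa, so the reported effects inherit the selection.

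At stake is the within-group part of a named secondary aim, the relative abundance of individual taxa. Taxa could be reported as changed under either bread although neither bread did anything.

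**Working it through.** The documents state no error rate for this rule, so there is no figure of theirs to reproduce.

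**Inputs.** List length 10 and the set-difference rule come from the document. The number of ranked taxa M and the correlation r over time of each taxon's test statistic are not given. I assume M from 15 to 300 and r from 0 to 0.99.

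**Step 1, unrelated rankings (r = 0), exact.** The probability that the two lists are identical is 1/C(M,10). The expected number of newly listed taxa is 10 × (1 − 10/M).
- M = 15: C(15,10) = 3003, so P(at least one change named) = 1 − 1/3003 = 0.9997, with 10 × (1 − 10/15) = 3.3 taxa newly listed.
- M = 300: the probability is 1 to many decimals, with 10 × (1 − 10/300) = 9.7 taxa newly listed.

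**Step 2, correlated statistics and no true change.** For each taxon, draw standard normal a at baseline and b = r·a + √(1 − r²)·e afterwards, with e an independent standard normal. Rank on absolute value, take ten each time and compare (4000 runs). Cells give the probability of at least one named change, then the mean number newly listed.

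| M | r = 0.8 | r = 0.95 | r = 0.99 |
|---|---|---|---|
| 15 | 0.99; 2.5 | 0.90; 1.5 | 0.62; 0.7 |
| 50 | 1.00; 4.5 | 0.98; 2.3 | 0.79; 1.1 |
| 100 | 1.00; 5.1 | 0.99; 2.7 | 0.86; 1.3 |
| 300 | 1.00; 6.0 | 1.00; 3.2 | 0.91; 1.5 |

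**Step 3, adding an entry filter.** Suppose a taxon must also pass FDR <.10 to enter a list.
- Nothing differs at either time: P(at least one named change) is 0.08 to 0.19 for r from 0 to 0.95.
- 20 of 100 taxa differ by the same true amount at both times (mean statistic 2, 3 or 4), so nothing changes: the probability is 0.95 to 1.00 for r up to 0.8, and 0.81 to 0.83 at r = 0.95.

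The filter therefore helps only when there is nothing to list. Once real and stable differences compete for ten places, noise decides which of them appear.

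**Step 4, gene cutoff.** An absolute log fold change of 1.1 is 2^1.1 = 2.14-fold if the base is 2, and e^1.1 = 3.00-fold if natural. The base is not stated.

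**The case against.** **The step is descriptive and the controlled comparison lies elsewhere.** This largely stands. The between-group DESeq2 comparison is separate, the FDR rule covers microbiome variables, and the secondary aims are framed against placebo bread. A reader might infer that the whole taxon-level outcome will report effects regardless of the bread. The documents do not support that: only the within-group results are affected. The rule still states which taxa changed, so calling it descriptive does not cure it.

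**The FDR threshold may be meant to govern entry to the lists.** The Statistical Analysis Plan section allows that reading, although the section with the rule does not state it. Under it the near-certain false finding disappears when nothing differs, but not when differences are stable (step 3).

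**The size rests on assumptions.** True. At r = 0.99 without a filter the probability falls to 0.62 to 0.91. The flaw itself does not depend on M or r.

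**Genes.** A reader might infer that genes are declared on fold change alone. The text does not support this: it names quasi-likelihood F tests and applies Benjamini-Hochberg to microbiome variables. Functional gene attributes also have a separate linear-model analysis for which no fold-change cutoff is stated. A reader might also infer that the cutoff misses the effect for which the trial is sized. That does not follow: the increase of about 22% in the Sample Size section is for the summed taxon composite, and no gene target is given. What remains is that the cutoff is not explicitly tied to the FDR threshold and has no log base.

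**Conclusion.** The concern holds for the within-group taxon rule, which is wrong as written. With lists always filled to ten and no true change, it names at least one changed taxon in about 90% to 100% of trials, with about 1.5 to 9.7 taxa newly listed. This assumes 15 to 300 taxa and correlations up to 0.95; at 0.99 the range is about 62% to 91%. With an FDR <.10 entry filter, which is not stated, it is about 8% to 19% when nothing differs and about 81% to 100% when 20 of 100 taxa differ equally at both times.

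The consequence is limited to secondary within-group taxon results. The primary composite, tested by Wilcoxon signed rank, is untouched, as is the separate between-group DESeq2 comparison. The gene cutoff needs a clarification only.

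**What to change.** - Delete the top-10 and set-difference steps.
- Test within-bread change directly for all taxa with a paired DESeq2 design (participant and time). Estimate the between-bread contrast with participant and period in the model.
- Declare taxa only by the rule already adopted, P<.05 with FDR <.10, and report log2 fold changes with intervals for every tested taxon, not only the selected ones.
- For genes, state that the 1.1 cutoff applies in addition to the FDR threshold of the quasi-likelihood F test, and give the log base.

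The cost is a re-run on existing data and probably a shorter list of changed taxa. The taxon section is written in the past tense, so the analysis may already have been run. If so, the replacement should be disclosed as a change made afterwards.
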